### Primary efficacy endpoint

The primary efficacy endpoint was the recurrence rate of atrial fibrillation. The recurrence of atrial fibrillation after ablation was statistically analysed from the following two perspectives

(1) The first recurrence of atrial fibrillation after the 90-day ablation period was used as the primary efficacy endpoint. Among them, the recurrence rate was defined as the duration of atrial fibrillation/flutter/atrial tachycardia recorded by ECG ≥30s from the end of the 3-month blackout period to the end of follow-up, which was considered as the recurrence of atrial fibrillation. The last postoperative follow-up was used as the follow-up endpoint for this analysis. Recurrence of atrial fibrillation during follow-up after surgery was defined as an event, absence of recurrence of atrial fibrillation was defined as censored, and the censored date was defined at the last date of follow-up. Persistent atrial fibrillation was defined as 24 Holter patients with total atrial fibrillation or 2 routine electrocardiograms with an interval of > 7 days, failure to spontaneously recurve, and no sinus rhythm electrocardiograms during hospitalization.

(2) 1-year recurrence of atrial fibrillation from 90 days after ablation to 1 year after surgery was used as the primary efficacy endpoint. Among them, the 1-year recurrence rate of atrial fibrillation was defined as the duration of atrial fibrillation/flutter/atrial tachycardia recorded by ECG ≥30s from the end of the 3-month blackout period to 1 year after surgery, which was considered as atrial fibrillation recurrence. 1 year after surgery was used as the end point of follow-up for this analysis. Recurrence of atrial fibrillation occurring after 1 year was defined censored, and the censored date was 365 days after surgery. Persistent atrial fibrillation was defined as 24 Holter patients with total atrial fibrillation or 2 routine electrocardiograms with an interval of >7 days, unable to spontaneously recurve, and no sinus rhythm electrocardiograms during hospitalization.

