(2) Primary efficacy endpoint: The recurrence rate of atrial fibrillation after ablation was statistically described in the two groups respectively.

Survival analysis was used to statistically analyse the recurrence rate of atrial fibrillation after ablation in the two groups. Kaplan-Meier curve of recurrence of atrial fibrillation after ablation was drawn between the two groups, and Log-rank test was used to compare the endpoint between the two groups. Besides, Cox proportional hazard regression model was used to calculate the risk ratio (HR) and 95% confidence interval (CI) of atrial fibrillation recurrence after ablation in the experimental group and the control group to estimate the efficacy, while considering each site as random effect included in the model.

- If atrial fibrillation recurred within 1 year, it was defined as the occurrence of end event. Time to recurrence of atrial fibrillation within 1 year=date of recurrence of atrial fibrillation-(date of radiofrequency ablation+90 days) +1, calculated by day.
- If the visit specified in the protocol was not completed within 1 year, the follow-up could not be completed by the end of 1 year due to loss of follow-up or withdrawal or other reasons, it was defined as censor, censor time=date of last follow-up-(date of radiofrequency ablation +90 days) +1, calculated in days.
- If the visit was completed within 1 year and no recurrence of atrial fibrillation occurred, it was defined as censor, and the censor time in analysis (1) was the date of last visit- (date of radiofrequency ablation+90 days) +1; The censor time in analysis (2) was 365 days.
- If the visits required by the protocol were completed within 1 year and AF recurred after 1 year, the endpoint was defined as event in analysis (1) and the recurrence time was the date of AF recurrence -(date of radiofrequency ablation+90 days) +1; the endpoint was defined as censor in analysis (2) and the censor time was the last visit- (date of radiofrequency ablation+90 days) +1.

(3) Secondary efficacy endpoints

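### In primary analysis (2) the censor time of event-free completers is a flat 365 days, but on the SAP's own clock, which starts 90 days after ablation, one year after surgery is day 276

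*SAP*

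**What the plan says.** Section 3.1.1 of the SAP (Primary efficacy endpoint) defines two primary analyses. Analysis (2) covers recurrence from 90 days after ablation to one year after surgery. Its horizon is explicit: "1 year after surgery was used as the end point of follow-up for this analysis". For patients whose first recurrence comes later it says: "Recurrence of atrial fibrillation occurring after 1 year was defined censored, and the censored date was 365 days after surgery".

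Section 6.4 (Analysis of efficacy, item 2) turns this into derived times in four bullets:

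- Recurrence within one year: "Time to recurrence of atrial fibrillation within 1 year=date of recurrence of atrial fibrillation-(date of radiofrequency ablation+90 days) +1".
- Follow-up of one year not completed: "censor time=date of last follow-up-(date of radiofrequency ablation +90 days) +1, calculated in days".
- Year completed without recurrence: for analysis (1), "the censor time in analysis (1) was the date of last visit- (date of radiofrequency ablation+90 days) +1"; for analysis (2), "The censor time in analysis (2) was 365 days".
- Year completed, recurrence afterwards: an event in analysis (1), but "the endpoint was defined as censor in analysis (2) and the censor time was the last visit", again less ablation plus 90 days, plus 1.

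These times feed the Kaplan-Meier curves, the log-rank test and the Cox model with site as a random effect.

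**The concern.** Every time rule in section 6.4 except one subtracts ablation date plus 90 days. The exception is the analysis (2) censor time for event-free completers, expected to be the largest group in the analysis. A bare 365 beside times counted from day 90 puts those patients on a different scale from everyone else. A programmer following the text would keep them at risk well past the date on which section 3.1.1 closes the endpoint. A completer last seen shortly before day 365 would also be carried as event-free beyond the last observation.

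The fourth bullet adds a second conflict. It censors recurrences after one year at the last visit with no upper limit, while section 3.1.1 fixes that date at 365 days after surgery. Patients who all passed one year without an event could therefore be censored at three different times. Within section 6.4, which rule applies depends on what happens after the endpoint window has closed. At stake are the correctness of the Kaplan-Meier display and whether a primary analysis can be reproduced from its written rules.

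**Working it through.** **Inputs.** The clock is date − (ablation date + 90) + 1 (section 6.4), so ablation + 90 is clock day 1. The end of analysis (2) is ablation + 365 (section 3.1.1). The stated censor time is 365 (section 6.4). The planning rates are 39.8% and 30% recurrence at one year, with 460 patients per arm and 20% loss (section 2.5).

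**Step 1: can 365 be reproduced?** The SAP's formula at ablation + 365 gives 365 − 90 + 1 = 276. Without the +1 it gives 275. Neither is 365, which appears only if days are counted from surgery; no other time rule in this part of section 6.4 does that.

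**Step 2: size of the mismatch.** 365 − 276 = 89 days. Clock day 365 is day 365 + 90 − 1 = 454 after ablation.

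**Step 3: the late-recurrence rule.** As an illustration, take a recurrence on day 380 and a last visit on day 400 after ablation. The recurrence is on clock day 380 − 90 + 1 = 291. The fourth bullet censors at 400 − 90 + 1 = 311, so the patient counts as event-free for 20 days after a known recurrence. Section 3.1.1 gives 276.

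**Step 4: effect on the planned test and estimates.** Under section 3.1.1 an event counts only up to ablation + 365, so every event falls on or before clock day 276. With the usual convention that a patient censored on an event day is still at risk that day, a completer is in every risk set whether censored at 276 or at 365. Late recurrences censored after day 276 are likewise in every risk set. The log-rank statistic, the Cox partial likelihood and the Kaplan-Meier estimate up to day 276 are therefore identical.

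One simulated trial confirms this. It assumed 460 per arm, exponential times giving 39.8% and 30% recurrence by clock day 276, about 20% uniform dropout, and no site effect:

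| Completers censored at | Events | Event-free completers | Log-rank chi-square | HR |
|---|---|---|---|---|
| 276 | 300 | 487 | 17.37 | 0.615 |
| 365 | 300 | 487 | 17.37 | 0.615 |

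What changes is the tail. With 365, all 487 completers appear at risk and event-free on clock days 277 to 365, where the correct number is zero.

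**Step 5: the conditional case.** Suppose clock day 365 were misread as the event window, and hazards stayed constant over the extra 89 days.

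- Active: hazard −ln(0.700)/275 = 0.001297 per day; extra recurrences 0.700 × (1 − exp(−0.001297 × 89)) = 7.6% of patients.
- Control: hazard −ln(0.602)/275 = 0.001845 per day; extra recurrences 0.602 × (1 − exp(−0.001845 × 89)) = 9.1% of patients.

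Section 3.1.1 contradicts that reading.

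**The case against.** The strongest reply is that nothing in the primary inference moves. Section 3.1.1 fixes the window, events after one year do not count, and Step 4 shows the same test statistic and hazard ratio with either value. This stands.

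A second reply is that 365 days may simply be shorthand for the date 365 days after surgery, in agreement with section 3.1.1. That is possible, since the sentence names no origin. But it defines a censor time, beside a day-90 formula for analysis (1), and under this reading the value to program is still 276. The reply changes the diagnosis from a wrong horizon to an omitted conversion; the correction is the same.

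A third reply is that capping completers at their last follow-up date is a separate choice, tied to visit windows that the protocol may define. This partly stands. Correcting the clock does not require the cap; the cap is justified because the flat value carries patients past their last observation.

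A reader might infer more: that the extra 89 days bias the hazard ratio or the P value, or that the endpoint really runs to day 454. The documents support neither. Section 3.1.1 states the end of follow-up, and the fourth bullet of section 6.4 itself treats recurrence after one year as censored in analysis (2).

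**Conclusion.** The inconsistency is real and should be fixed, but it is not critical. The flat 365 does not fit the clock used around it: the value matching section 3.1.1 is 276, a difference of 89 days per event-free completer. The last-visit rule for late recurrences contradicts section 3.1.1.

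The consequences are a false event-free plateau and wrong numbers at risk on clock days 277 to 365, and conflicting censoring rules for one primary analysis. Replacing 365 by 276 leaves the log-rank P value, the hazard ratio and the curve up to day 276 unchanged, provided events are limited to one year after surgery as section 3.1.1 states. That result follows from the risk sets and does not depend on the simulation's assumptions.

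The 7.6% and 9.1% extra recurrences are not an expected effect. They show only what a misprogrammed event window would admit, assuming constant hazards.

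**What to change.** State one rule for analysis (2) in section 6.4:

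- Event only if the first recurrence after the blanking period is on or before ablation date + 365; time = recurrence date − (ablation date + 90) + 1.
- Everyone else is censored at min(last follow-up date, ablation date + 365) − (ablation date + 90) + 1, with a maximum of 276.

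Delete the flat 365 days and the last-visit rule for recurrences after one year, and say in the first bullet that the year is counted from ablation. Analysis (1) needs no change.

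The cost is a few words in the SAP and one derivation line. The cap at last follow-up can alter risk sets slightly for completers seen before day 365. By how much depends on visit timing, which the SAP does not give, so the rule should be settled while the data are still blinded.

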## Sample Size

Referred to《Catheter ablation vs. antiarrhythmic drug treatment of persistent atrial fibrillation: a multicentre, randomized, controlled trial (SARA study)》(European Heart Journal, 2014 Volume 35, Issue 8, Pages 501-507).

Assumed the 1-year recurrence rate of patients with persistent AF after radiofrequency ablation is 39.8% (the duration of an episode of AF/flutter/atrial tachycardia recorded by ECG≥30s 3 months after ablation is considered as a recurrence of AF). We predicted that the 1-year recurrence rate of atrial fibrillation could be reduced to 30% by adding Shensong Yangxin capsule after radiofrequency ablation. Therefore, we may expect that sample size of minimum 368 patients in each study group will provide the study with 80% power to detect a difference in primary outcome at 5% of significance. Accounting for 20% of lost to follow up patients of the trial, we need to include 460 patients in each group and the total sample size is 920.

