## Treatment

**Teat Group:** conventional treatment+ Shensong Yangxin capsule 4 capsules/times, 3 times/day, orally.

**Control Group:** conventional treatment + Shensong Yangxin capsule placebo 4 capsules/times, 3 times/day, orally.

All the above treatments were performed after radiofrequency ablation, and the course of treatment was 1 year

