With reference to most literatures, the current assessment of recurrence of atrial fibrillation after ablation is mainly based on Holter electrocardiogram (ECG), remote electrocardiogram or the patient's symptoms. In this study, 24h-holter electrocardiogram and electrocardiogram will be used as monitoring means to evaluate recurrence of atrial fibrillation after radiofrequency ablation based on each visit of the patient at the follow-up point and the patient's symptoms.

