# Statistical analysis Methods

General principles of statistical analysis

Statisticians are responsible for developing a statistical analysis plan (SAP) with the principal investigator after the protocol is confirmed. Statistical analysis will be performed with SAS 9.4 (or higher version; SAS Institute, Cary, NC). The sample size is calculated using PASS13 software (NCSS, Kaysville, UT).

A 2-tailed P<0.05 will be considered statistically significant in all statistical tests. (If no other specification). No adjustments for multiple comparisons were made.

Qualitative data will be described with frequencies and percentages; quantitative data will be described with mean and standard error or with median and interquartile interval, minimum and maximum.

Continuous variables will be summarized with mean and SD and compared using paired t-test or Wilcoxon rank test, as appropriate. Categorical variables will be summarized with frequencies and percentages and compared using chi-square test or Fisher exact test, as appropriate. Ranked variables will be compared using Wilcoxon rank test or CMH test.

Enrolment Analysis

Enrollment analysis will summarize the number of enrollment and the number of subjects who completed the trial of each site and lists dropout subjects.

The dataset size between groups, subjects' disposition between sites, dropout rate and termination reasons will be listed in detail

Baseline and demographic characteristics

Baseline characteristics of patients will be described overall and per group.

Demographic and baseline characteristics (age, gender, height, BMI, vital signs, etc.), medical history, family history of atrial fibrillation, drug allergy, etc. of the subjects will be summarized. T-test or Wilcoxon rank-sum test will be used in baseline comparison of continuous variables such as age, height, and BMI between the two groups. The chi-square test or Fisher’s exact test will be used in the baseline comparison of categorical variables such as gender, and medical history

Analysis of efficacy

Both mITT and PPS were used for effectiveness analysis. Analysis performed on PP populations using the same methods can be considered as a sensitivity analysis.

(1) Baseline: The baseline of each relevant efficacy endpoints was described. For comparison methods between groups, refer to the general statistical method above.

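### Primary analysis (1) counts recurrences after the required visits without an upper time limit but fixes no matching end of follow-up for event-free patients, so follow-up after 1 year can depend on the outcome

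*SAP*

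**What the plan says.** SAP section 6.4, item (2), gives the derivation rules for the primary endpoint. Two of them matter here, both for analysis (1).

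- Late relapse: "If the visits required by the protocol were completed within 1 year and AF recurred after 1 year, the endpoint was defined as event". The time runs from day 90 after ablation to the date of recurrence, and no latest date is given.
- No relapse: for a patient who completed the visits, "the censor time in analysis (1) was the date of last visit- (date of radiofrequency ablation+90 days) +1".

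Section 3.1.1(1) describes the end of observation only in general terms: "The last postoperative follow-up was used as the follow-up endpoint for this analysis". It names no common cut-off date and no scheduled contact after 1 year. The same section says that recurrence is assessed by ECG and 24-hour Holter, "based on each visit of the patient at the follow-up point and the patient's symptoms". On treatment, section 2.7 states: "All the above treatments were performed after radiofrequency ablation, and the course of treatment was 1 year".

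Analysis (2) censors recurrences after 1 year. Both analyses are called the primary efficacy endpoint, and both use Kaplan-Meier, log-rank and Cox methods.

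**The concern.** The two rules start from the same group: patients who have completed the required visits. A patient who later relapses, and whose relapse comes to light, gains follow-up time up to the relapse. A patient who does not relapse stops at the last visit. If nobody arranges to see the event-free patients again, being at risk after that visit depends on having the event. Kaplan-Meier, log-rank and Cox methods all assume that follow-up does not depend on the outcome in this way. Because symptoms can prompt an assessment, relapsers have a route back into the data that event-free patients lack.

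Two results of analysis (1) are at stake. The first is the recurrence rate at the end of follow-up, read from the tail of the curve. The second is the hazard ratio with its log-rank test: late events compare relapsers mainly with other relapsers, carry little information on treatment, and pull the estimate towards 1. This is separate from the question of having two primary analyses; it would arise if analysis (1) were the only one.

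**Working it through.** **Inputs from the SAP.** 1-year recurrence 39.8% versus 30%; 368 per arm, or 460 per arm after 20% loss (section 2.5); "80% power to detect a difference in primary outcome at 5% of significance" (section 2.5); "A 2-tailed P<0.05 will be considered statistically significant in all statistical tests" (section 6.1).

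**The plan's own figure.** With unpooled variance, n = (1.960 + 0.842)² × (0.398×0.602 + 0.30×0.70) / 0.098² = 7.849 × 0.4496 / 0.009604, which rounds up to 368. Then 368 / 0.80 = 460. Both are reproduced.

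**Implied hazard ratio.** ln(0.70) / ln(0.602) = 0.3567 / 0.5075 = 0.703.

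**Why the tail goes to 100%.** Each Kaplan-Meier step multiplies the survival estimate by (1 − events / number at risk). Once the last event-free completer has been censored, everyone still at risk is a future event. The last of them gives the factor 1 − 1/1 = 0, so estimated recurrence is 100% however few late events there are.

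**Simulation at the enrolled size.** 460 per arm; constant hazard from day 90; 365 − 90 + 1 = 276 days to 1 year; 20% dropout; 1-year visit 0 to 14 days after the 1-year point; 1,500 runs; site effect omitted. The treatment hazard ratio is held at 0.703 after 1 year, so any shift comes from the follow-up rule alone. Monte Carlo error on power is about √(0.8×0.2/1500) = 1 point. The number of late relapses is not in the SAP, so a range is shown.

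No follow-up of event-free patients after the 1-year visit:

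| Late relapses recorded | Late events | HR, all censored at 1 year | HR, as written | Power, 1 year / as written | Final KM, control / treated |
|---|---|---|---|---|---|
| All, 365 days, same hazard | 200 | 0.706 | 0.791 | 83.5% / 72.3% | 100% / 100% |
| Half, 365 days, same hazard | 100 | 0.701 | 0.756 | 86.1% / 78.5% | 100% / 100% |
| All, 180 days, same hazard | 111 | 0.703 | 0.766 | 84.4% / 75.7% | 100% / 100% |
| All, 180 days, 30% of the hazard | 37 | 0.700 | 0.724 | 86.6% / 82.6% | 100% / 100% |
| Half, 90 days, 30% of the hazard | 9 | 0.700 | 0.705 | 84.7% / 84.3% | 99.5% / 98.5% |

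The shift in hazard ratio is thus 0.705 − 0.700 = 0.005 at the low end and 0.791 − 0.706 = 0.085, about 0.09, at the high end.

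With a share of event-free completers also followed for 365 more days (same hazard, all relapses recorded):

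| Share followed | HR, as written | Final KM, control / treated |
|---|---|---|
| 10% | 0.760 | 94% / 90% |
| 50% | 0.718 | 79% / 68% |
| 90% | 0.707 | 71% / 58% |
| 100% (unbiased) | 0.703 | 69% / 56% |

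**At 368 per arm without dropout.** With half of the relapses over 180 days recorded and no event-free follow-up, HR is about 0.74 instead of 0.70 and power about 74% instead of 80%. With about 6 late events in total, HR is 0.706 instead of 0.703 and power 79% instead of 80%.

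**The benign case, 368 per arm.** Suppose every patient attends one last visit and late recurrences are found only there. With last visits on days 351 to 395, HR is 0.704 against 0.705 when truncated at day 365, and power is 81% against 80%. With last visits on days 365 to 425, HR is 0.704 in both, and power is 84% against 80%.

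**The case against.** The strongest reply is that the harmful premise is inferred. No passage says that event-free patients go unseen after 1 year. Section 3.1.1(1) ends analysis (1) at the last postoperative follow-up for everyone. Section 6.4 distinguishes the last visit in analysis (1) from a fixed 365 days in analysis (2), which suggests that some follow-up beyond day 365 was expected. The 1-year assessments are timed from treatment and treatment starts after ablation, so a 1-year visit may fall after day 365 from surgery. Visit windows and later visits belong to the protocol, which is not at hand. On that reading there is no bias, and late events even add power.

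This stands, and it makes the point conditional. It does not remove it: the late-relapse rule speaks of patients whose required visits are already complete within 1 year, and nothing in the SAP obliges equal follow-up after that. Partial follow-up does not cure the problem, as the 10% and 50% rows show.

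A second reply is that the power cost is small, since 78.5% at the enrolled size is close to the planned 80%. The fair comparison is the same data censored at 1 year, which gives 86.1%. It is true, though, that with few late events the hazard ratio hardly moves and only the tail of the curve fails.

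A reader might also infer that one arm could return more often for unscheduled ECGs and so bias the comparison. The trial is double-blind, and the SAP gives no ground for expecting this.

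**Conclusion.** The rule for analysis (1) needs correcting, but the harm is conditional on follow-up that the SAP does not fix. If event-free patients are not followed equally beyond 1 year, the tail of the curve and the end-of-follow-up recurrence rate drift towards 100%, and the hazard ratio moves towards 1 by about 0.005 to 0.09. Power at 368 per arm falls from about 80% to about 74% with half of the relapses over 180 days recorded. These sizes assume a constant hazard from day 90 and, in the larger cases, the same hazard after 1 year. The number of late relapses and the extent of later event-free follow-up are assumptions.

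It is tempting to conclude that analysis (1) as a whole is uninterpretable, or that it could produce a false positive. The documents support neither. The curve up to 1 year is essentially unaffected. Analysis (2), which matches the 1-year rate behind the sample size, does not have this fault. The bias is towards no effect, and under blinding the recording of late relapses should not depend on arm, so type I error is not inflated.

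**What to change.** In sections 3.1.1(1) and 6.4(2), apply one end-of-follow-up rule to events and censoring alike in analysis (1):

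- Count a recurrence as an event only if it is recorded on or before the patient's last scheduled rhythm assessment. That is the 1-year visit, even if held after day 365, or a later common cut-off date if all patients have scheduled follow-up to it.
- Censor event-free patients at that same point.
- List recurrences first recorded after it by arm, descriptively only.

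Unconditional truncation at day 365 is not needed: it would discard valid events wherever follow-up is equal.

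The cost is SAP wording and a changed derivation of event and censoring dates, with no new data. A few late recurrences leave the event count. If no scheduled follow-up exists after the 1-year visit, analysis (1) becomes close to analysis (2).

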### Secondary efficacy endpoints

(1) Changes in atrial fibrillation load at 3 months, 6 months, and 1 year after treatment. Atrial fibrillation load was defined as the longest duration of atrial fibrillation episodes, the number of episodes of atrial fibrillation, and the percentage of time patients were in atrial fibrillation during a given monitoring period.

(2) Time of first occurrence of atrial flutter/atrial fibrillation.

(3) Incidence of electrical cardioversion within 1 year after treatment.

(4) Changes of transthoracic echocardiographic indexes at 1 year after treatment.

(5) Incidence of stroke and thromboembolism at 6 months and 1 year after treatment.

(6) Health Survey Summary Form (SF-36) score within 1 year after treatment.

Safety endpoints

(1) Adverse events (AEs): Any adverse medical events occurring between the time subjects signed the informed consent and were enrolled in the study and the last follow -up, regardless of whether there was a causal relationship with the study drug, was considered an adverse event. The sum of "definitely relevant", "possibly relevant" and "unascertainable" associated with the study drug was the adverse reactions (ADRs) of the study drug, and the incidence of adverse reaction was calculated accordingly.

(2) Laboratory indicators: blood routine, urine routine, stool routine, biochemical examination and coagulation function examination;

(3) Clinical physical examination and vitals.

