# Processing of missing data

In this study, survival analysis was used to analyse the 1-year recurrence of atrial fibrillation for the primary efficacy endpoint. mITT and PPS were both included for the patients who failed to complete the 1-year follow-up due to half-way drop out or missing follow-up. The endpoint was defined as censored in the statistical analysis, and the censored date was the last follow-up date. No carry-over of missing data or multiple fillings of missing data were performed.

Missing data of secondary endpoints and safety endpoints, no filling or other processing is carried out.

Handling of dates: When only part of the date is known, the following rules are used to calculate the duration. If the start time (such as the date of first onset of AF or the date of diagnosis) is partially missing and only the day is missing, then fill in the first day of the corresponding month. If the end date is partially missing and only the day is missing, replace it with the last day of the month. If both the day and month of the date are missing, this date is treated as missing.

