Aimed at changes in atrial fibrillation load at 3 months, 6 months and 1 year after treatment, the mean, standard deviation, median, minimum, maximum, lower quartile (Q1) and upper quartile (Q3) of atrial fibrillation load at each visit site were calculated according to the form of quantitative endpoints. T-test or Wilcoxon rank sum test were used to compare it between the two groups. At the same time, the changes of atrial fibrillation load compared with baseline at 3 months, 6 months and 1 year after treatment were statistically described, and T-test or Wilcoxon rank sum test was used to compare the changes between the two groups.

The time of the first occurrence of atrial fibrillation/atrial fibrillation was analysed as the secondary endpoint. The occurrence days of atrial fibrillation/atrial fibrillation were calculated by the date of radiofrequency ablation surgery as the starting date, the occurrence days= the date of the first occurrence of atrial fibrillation/atrial fibrillation-the date of radiofrequency ablation surgery +1. For patients with atrial flutter/atrial fibrillation, the mean, standard deviation, median, minimum, maximum, lower quartile (Q1) and upper quartile (Q3) of occurrence time were calculated according to the form of quantitative variables. T-test or Wilcoxon rank sum test were used to compare the occurrence time between the two groups.

The secondary efficacy endpoint of transthoracic echocardiography one year after treatment were analysed. The indexes of transthoracic echocardiography mainly included left ventricular end-diastolic volume, left ventricular end-systolic volume, ejection fraction, stroke volume, cardiac output and other evaluation indexes. The mean, standard deviation, median, minimum, maximum, lower quartile (Q1) and upper quartile (Q3) of the results of the evaluation indicators were calculated according to the form of quantitative variables, and T-test or Wilcoxon rank sum test were used to compare the evaluation variables between the two groups.

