The incidence of cardiac cardioversion within 1 year after treatment and the incidence of stroke and thromboembolism at 6 months and 1 year after treatment were analysed as secondary efficacy endpoints. The incidence and incidence difference of the two groups in the experimental group and the control group were described according to general principles. Meanwhile, Chi-square test or Fisher exact probability method were used to compare the incidence between the two groups.

SF-36 score within 1 year after treatment were analysed, and the mean, standard deviation, median, minimum, maximum, lower quartile (Q1) and upper quartile (Q3) of each dimension score were calculated according to the form of quantitative endpoints. And T-test or Wilcoxon rank sum test were used to compare the scores of each dimension between the two groups. It includes 8 dimensions and an overall score. The score of each dimension is calculated as follows:

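### Time to first AF/flutter is tested only in patients who had the event, without censoring, so the secondary comparison is not randomised and has almost no power

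*SAP*

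**What the plan says.** SAP section 3.1.2 lists as secondary endpoint (2): "Time of first occurrence of atrial flutter/atrial fibrillation". Section 6.4, item (3), says how it is analysed:

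- Occurrence days "were calculated by the date of radiofrequency ablation surgery as the starting date", as the date of first occurrence minus the date of ablation, plus 1.
- The descriptive statistics are restricted: "For patients with atrial flutter/atrial fibrillation, the mean, standard deviation, median", and so on through the quartiles.
- The next sentence gives the test: "T-test or Wilcoxon rank sum test were used to compare the occurrence time between the two groups".

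No sentence assigns a time or a censoring date to a patient without an event. Section 5 adds: "Missing data of secondary endpoints and safety endpoints, no filling or other processing is carried out".

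For the primary endpoint, section 6.4, item (2), draws Kaplan-Meier curves, fits a Cox model with site as random effect, sets out event and censoring rules, and states: "Log-rank test was used to compare the endpoint between the two groups".

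**The concern.** The test sentence does not repeat the restriction to patients with an event, but the variable is defined only for them, so the test can use no one else. Having an event is a post-randomisation outcome that the drug is intended to change. Patients with events in one arm are therefore not comparable, by randomisation, with patients with events in the other. The question becomes when recurrences happened among those who recurred, not whether treatment delays recurrence.

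Two things are at stake. A drug that lowers the hazard evenly leaves the event-only times almost unchanged, so the test will usually miss a real effect. A drug that mainly removes late recurrences leaves the early ones behind, and its event times then look shorter than on placebo. The resulting P value would be read at the two-sided 0.05 level of section 6.1 and could appear to contradict the primary result.

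**Working it through.** **Inputs from the SAP.** Section 2.5: control 1-year recurrence 39.8%, treated 30%, 368 per group for 80% power at 5%, 460 per group after 20% loss. Section 6.1: two-sided 0.05. Section 2.6: 1:1 allocation.

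**The plan's own figure.** With unpooled variance, n = (1.960 + 0.842)² × (0.398×0.602 + 0.30×0.70) / 0.098² = 7.849 × 0.4496 / 0.009604 = 367.4, so 368 per group. Then 368/0.80 = 460 per group and 920 in total. The plan's figures reproduce.

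**Who is left in the test.** Expected events are 368×0.398 = 146 in control and 368×0.30 = 110 on treatment, 257 in all. The other 479 of 736 patients (65%) contribute nothing, and more of them come from the better arm.

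**What a log-rank test would give.** HR = ln 0.70 / ln 0.602 = 0.3567/0.5075 = 0.703. By Schoenfeld, power = Φ(√257/2 × 0.3527 − 1.96) = Φ(0.87) = 81%. With 460 per arm (321 events) it is Φ(1.20) = 88%.

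**Simulation.** There were 4000 trials per scenario, with the plan's rates and no loss. The hazard shapes are assumptions, because the SAP states none. Monte Carlo error is up to about 0.8 percentage points (√(0.25/4000)), and repeat runs differed by up to two points.

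(A) *Proportional hazards.* At 368 per arm, event-only mean times are 168 (control) and 172 days (treated) if the hazard runs from ablation, and 216 and 220 if it starts at day 90. The event-only test rejects in about 6-8% of trials. Log-rank rejects in 79-81% at 368 per arm and 87-88% at 460. The treated mean is the shorter one in 36-38% of trials at 368 per arm.

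(B) *Late effect.* The 1-year rates are unchanged. Hazards are equal until day s of the 275-day post-blanking window and reduced afterwards by the ratio that restores 30%: HR_late = (0.3567 − 0.5075·s/275) / (0.5075·(275−s)/275).

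| Onset s (day) | HR_late | Wilcoxon significant in the wrong direction, 368 per arm | 460 per arm |
|---|---|---|---|
| 60 | 0.62 | about 16-18% | about 20-21% |
| 90 | 0.56 | about 37% | about 44% |
| 137.5 | 0.41 | about 69-70% | about 79-80% |
| 160 | 0.29 | about 82% | about 89% |

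At onset day 90 with 368 per arm, event-only means are 217 (control) and 201 days (treated), while log-rank on all patients shows benefit in 74% of trials.

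(C) *Blanking-period episodes counted.* The clock starts at ablation, so the formula admits them. Suppose 10-30% of each arm has an episode by day 90, unaffected by the drug, and the plan's rates apply afterwards (368 per arm). The treated mean is then the shorter one in 71-85% of trials, and Wilcoxon is significant in the wrong direction in 8-20%. More patients now have events, so the share dropped falls to about 59-46%. Log-rank power also falls, to 65%, 49% and 34% at 10%, 20% and 30%. The counting rule therefore matters whichever test is used.

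(D) *Early effect only.* At 368 per arm the event-only test shows benefit in over 99% of trials. The direction of its result depends on when the drug acts.

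**The case against.** The best defence is that this is one secondary endpoint of six. The primary endpoint covers AF, flutter and atrial tachycardia after day 90 and is analysed with proper survival methods, so a valid time-to-event comparison of largely the same arrhythmia will be reported anyway. That stands, and it limits the severity. It does not make the event-only test valid.

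It can also be said that the direction reversal rests on hazard shapes the SAP does not state. That stands too. A reader might infer that the planned test will generally make a beneficial drug look harmful. The documents do not support this: under proportional hazards the average direction is correct and the damage is lost power, and an early effect points the right way. No single reversal figure should be quoted without its onset assumption. In addition, scenario (B) uses the post-blanking window, whereas the endpoint as written runs from ablation; scenario (C) addresses that difference.

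A reader might extend the criticism to cardioversion, stroke and thromboembolism, for which section 6.4 states: "Chi-square test or Fisher exact probability method were used to compare the incidence between the two groups". That does not follow. Those endpoints are defined as incidences over fixed periods, the comparison does not select patients on having the event, and a test of proportions is a standard analysis. How patients lost early enter the denominator is a separate, milder question, not quantified here.

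**Conclusion.** The analysis of this endpoint is wrong as written and should be fixed. The selection on outcome follows from the text alone, with no modelling. The 65% loss follows from the plan's rates if only post-blanking events count. The contrast of about 6-8% against about 80% power at 368 per arm (about 87% for log-rank at 460) rests on proportional hazards and no loss. Wrong-direction significance of about 16-82% at 368 per arm, or 20-89% at 460, rests on an assumed late effect starting between day 60 and day 160 of the 275-day window; it is a conditional range, not a forecast. A reader might take this as a threat to the trial's main conclusion. It is not one, because the primary analysis keeps all patients in its analysis set and censors them explicitly.

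**What to change.** In SAP section 6.4, item (3), replace the test for this endpoint as follows:

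- Analyse time from ablation to first AF/flutter in all mITT patients by Kaplan-Meier, log-rank and the Cox model with site as random effect.
- Censor event-free patients at the earlier of last follow-up and day 365.
- State whether episodes in the 90-day blanking period count as events. Section 4 excludes patients who did not complete that period, but it does not settle the status of episodes within it.
- Keep the summary of occurrence times among patients with events as description, without a test.
- Correct the endpoint name in that paragraph, where fibrillation is written twice, apparently for flutter/fibrillation.

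The cost is a few sentences before database lock and one derived variable. The methods are already in the plan for the primary endpoint, but its clock starts 90 days after ablation, so the time derivation cannot be reused unchanged. No new data are needed.
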